### Register-based control group

In addition to the randomized controls, data from the Swedish National Child Obesity Treatment Register BORIS, started in 2005 [55], will be collected retrospectively to enable a national comparison of the effect of standard treatment to the ML program for children with obesity. Data from children in the BORIS registry will be selected randomly in a 1:3 ratio matched to children with obesity in the intervention arm on age (± 100 days), sex, BMI z-score at baseline and year of treatment initiation. The type of care received will be documented retrospectively over a period of 12 months based on registry data.

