### Data analysis

All analyses will be performed as an intention-to-treat analysis. Descriptive statistics will be used to summarize participant characteristics at baseline per study arm. Prior to analysis, the distribution of the outcomes will be assessed for normality and homogeneity. Between arm differences for outcomes, BMI z-score (primary outcome), %IOTF-25, probability of reaching BMI z-score cut-offs and WHtR will be analyzed.

To analyse the primary outcome of BMI z-score we will fit a linear mixed model with BMI z-score at 0, 3, and 12 months as the outcome variable, including a random intercept for each child. Fixed covariates will be treatment assignment (ML or control), time (in months), their interaction, and baseline weight status. The effect of the treatment will be assessed by the interaction parameter, which is interpreted as the difference in change of BMI z-score per month” between the two randomisation arms. A dose-effect analysis will be performed to assess the effect of number of ML sessions attended. This will be performed by replacing the treatment variable in the regression model with a variable indicating how many sessions the child’s parents attended.

The register control arm will be compared against the ML arm regarding BMI z-score, %IOTF-25, probability of reaching BMI z-score cut-offs and WHtR, using the same methods as described above adjusted for confounders. Secondary outcomes will be analyzed using the same principles as above. Interviews with parents and HCP will be transcribed verbatim and analyzed using reflexive thematic analysis [73–75]. We will explore causal pathways between effectiveness- and implementation outcomes by integrating the quantitative and qualitative data. Missing data will be evaluated for its extent and patterns. If missingness in key outcomes (e.g., BMI z-score, %IOTF-25, BMI z-score cut-offs, WHtR) exceeds a predefined threshold, appropriate statistical methods such as multiple imputation will be applied. Full details about the analysis will be described in the Statistical Analysis Plan, which will be finalized and published in Clinicaltrials.gov before the end of data collection.

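### In the register comparison, confounders added to the trial's random-intercept model as main effects would leave the arm-by-time estimate for BMI z-score essentially unadjusted

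*Protocol article*

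**What the plan says.** Under Register-based control group, the protocol article says that register children "selected randomly in a 1:3 ratio matched to children with obesity in the intervention arm on age" (within 100 days), together with "sex, BMI z-score at baseline and year of treatment initiation". The comparison is additional to the randomised one and is limited to children with obesity.

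Under Data analysis, the trial model for BMI z-score is a linear mixed model of the values at 0, 3 and 12 months, "including a random intercept for each child". On the fixed part: "Fixed covariates will be treatment assignment (ML or control), time (in months), their interaction, and baseline weight status". On the effect: "The effect of the treatment will be assessed by the interaction parameter", read as a difference in change per month.

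The same section then sets the ML arm against the register children on BMI z-score, WHtR, %IOTF-25 and the cut-off probabilities. The method is given only as "using the same methods as described above adjusted for confounders". It does not name the confounders, say whether they enter alone or with time, or mention the matched set. Full details are left to a statistical analysis plan that is still to be finalised.

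**The concern.** In the randomised comparison, allocation protects the slope contrast, so it matters little whether covariates can act on it. The register comparison has no such protection beyond its four matching variables. Everything else that differs between one municipality and a national register, and that also affects change in BMI z-score, has to be handled by the stated adjustment.

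The article gives reason to expect such differences. The Background describes a pronounced social gradient in overweight and a higher burden among people born outside Europe. Study setting puts the share of inhabitants born abroad at more than 44%, twice the national figure. Neither social position nor country of birth is a matching variable.

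If the confounders are added as baseline weight status is, the adjustment does not touch the reported effect. A difference in case mix could then be reported as an adjusted ML effect.

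**Working it through.** **The plan's own figure.** The article gives no sample size for the register comparison. The trial figure reproduces: n per arm = 2 × (1.960 + 0.842)² × 0.3² / 0.16² = 55.2, so 56. Then 56 / 0.9 = 62.2, so 63 per arm and 126 in total.

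**Why a main effect is inert.** With visits at 0, 3 and 12 months the mean time is 5, and the centred times are −5, −2 and 7. Their squares sum to 25 + 4 + 49 = 78. In a random-intercept model with complete data, the arm-by-time estimate is the difference between arms in the mean child slope, where

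slope = (−5·y₀ − 2·y₃ + 7·y₁₂) / 78.

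A time-constant covariate adds the same amount c to all three values. It changes the slope by c × (−5 − 2 + 7) / 78 = 0. The estimate cannot move, whatever the covariate.

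**Simulation check.** Assumptions: 60 sets of one ML and three register children; true 12-month difference −0.16; one unmatched confounder with a mean 0.5 SD higher in the ML arm and an effect on slope of −0.006 per month per SD; 40 runs. The expected 12-month bias is 0.5 × (−0.006) × 12 = −0.036.

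| Data | No covariates | Main effects | Covariate × time | Largest shift from main effects |
|---|---|---|---|---|
| Complete | −0.199 | −0.199 | −0.166 | 0.000000 |
| 20% of follow-up visits missing | −0.196 | −0.196 | −0.163 | 0.0015 |
| 20% missing, irregular timing | −0.206 | −0.206 | −0.167 | 0.0015 |

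A separate simulation (32 ML and 96 register children) gave agreement to about 1e-14 with complete data and a shift of at most 0.003 with 10% missing visits. In both simulations, only covariate-by-time terms removed most of the bias.

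**Size of the bias, as illustration only.** Bias in 12-month change = difference in confounder prevalence × difference in change between confounder levels. Take 44% against 22% (half of 44%, from Study setting). A difference in change of 0.1 gives 0.22 × 0.1 = 0.022, or 14% of 0.16. A difference of 0.2 gives 0.044, or 28%. The 0.1 and 0.2 are assumptions with no source in the article.

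**Does the matching survive?** A model without set term or covariates gave −0.160 under matched sampling, which is the truth, and −0.195 under unmatched sampling. The matching is done by the sampling and does not depend on the model.

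**What ignoring the sets costs.** In the simulation, the slope model's mean standard error was 0.025 against a true sampling SD of 0.021. For simple 12-month change it was 0.033 ignoring sets and 0.021 respecting them. In closed form, let ρ be the within-set correlation of change:

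- true variance = 0.3² × (1 − ρ) × (4/3) / n
- variance assumed when sets are ignored = 0.3² × (4/3) / n

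Assume n = 28 sets (about half of 63 × 0.9 = 56.7 ML children) and read the 0.3 as the SD of 12-month change. The assumed standard error is 0.0655. Normal approximation, two-sided 5%, difference 0.16:

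| ρ | True SE | Power, sets ignored | Power, sets used | Type I error, sets ignored |
|---|---|---|---|---|
| 0.05 | 0.0638 | 69% | 71% | 4.4% |
| 0.2 | 0.0586 | 71% | 78% | 2.8% |
| 0.5 | 0.0463 | 75% | 93% | 0.6% |

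A t reference on 83 degrees of freedom (112 children − 28 sets − 1) puts the set-aware figures at 70%, 77% and 93%. The article gives no ρ.

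**Cut-off outcomes.** In a logistic model for a reduction of at least 0.25, main-effect adjustment moved the arm log-odds ratio from 1.42 to 1.60. Here it does act.

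**The case against.** The strongest reply is that the article never says the confounders are main effects. That form is read across from baseline weight status, and confounder-by-time terms would also fit the sentence. The template cannot even be carried over literally: the comparison is limited to children with obesity, so a term for overweight versus obesity would be constant. The sentence may therefore be shorthand, with confounders, interactions and set handling left to the analysis plan.

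Part of this stands. The main-effects form is an inference, and a missing confounder list or set term is not in itself an error in an article. But the article does fix the model and the effect parameter, and together they make the most natural form of adjustment ineffective. An analysis plan that followed the text faithfully would inherit the problem.

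A reader might go further and infer that the comparison is in effect unmatched and unadjusted. The documents do not support that. Sampling balances age, sex, baseline BMI z-score and year of treatment initiation whatever model follows. Ignoring the sets errs on the conservative side when changes correlate positively within sets. The cut-off outcomes respond to main-effect adjustment.

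Nor should the 0.022 to 0.044 be taken as an estimate. The 44% describes all inhabitants, not ML families, and it is set against the general population, not an obesity register. The register may itself contain more families of migrant background, which would narrow the gap. Finally, the comparison supplements the randomised one and does not affect the primary analysis.

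**Conclusion.** The point holds in a limited form. If confounders enter the stated model as baseline weight status does, adjustment leaves the BMI z-score slope contrast exactly unchanged with complete data at common visit times, and practically unchanged otherwise (at most 0.003 over 12 months in the cases simulated). The same applies to %IOTF-25 and WHtR if they are analysed with that model. It does not apply to the cut-off probabilities.

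The consequence is a non-randomised comparison described as adjusted while differences in change from unmatched factors remain. The size of the resulting bias cannot be derived from the documents. Leaving out the matched sets is a secondary matter of efficiency. Under the assumptions used, the power loss is about 2 points at a correlation of 0.05, 7 at 0.2 and 18 at 0.5, and the type I error stays below 5%.

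**What to change.** For the register comparison, replace the reference to the methods above with a stated model in which confounders act on change. Either of these would do for BMI z-score, %IOTF-25 and WHtR:

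- a model for the 12-month value on arm, baseline value and the confounders available in both sources; or
- the longitudinal model with confounder-by-time terms added, and the arm contrast taken from that model.

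In either case use a set-aware standard error: a matched-set effect in the 12-month model, or a set-level slope in the longitudinal one. For the BMI z-score cut-offs, use conditional or set-clustered logistic regression.

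The cost is wording in an analysis plan that is not yet final, a few model terms and a few degrees of freedom. If the set is a fixed effect, sets without an analysable ML child drop out. Adjustment can reach only confounders that the register also records. The article collects country of birth and education by parent questionnaire and does not say whether the register holds them. The plan should list which confounders exist in both sources and state that the rest remain uncontrolled.

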### Control arm: standard care for overweight or obesity

Standard care for overweight [54] and obesity [25] is based on national guidelines (Table 1) where children with obesity are referred to a pediatrician for yearly check-ups often in combination with follow-up visits to a pediatric nurse, dietician and/or physiotherapist. For some children, referral to a psychologist can also be part of obesity treatment. They also have the option to receive a digital support tool. For children with overweight, parents are offered referral to the PHC for support by a dietitian and physiotherapist. All children’s weight, height, and waist circumference will be measured on three occasions (Fig. 2). A timeline of the study procedures is illustrated in Fig. 2.

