### Sample size

We estimate that the trial will need 126 children (63 children in the intervention and 63 in the control group) to be able to detect a difference at 12 months between the groups in BMI z-score of -0.16 with a standard deviation of 0.3, 80% power and an alpha level of 0.05, including an estimated 10% loss to follow-up.

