### Data collection

Data collection activities, time points, and data sources are shown in Table 4. Children’s height, weight, and waist circumference will be measured by the school nurse at three timepoints. Parents will answer a baseline questionnaire including demographic data (sex, age, country of birth, years in Sweden, education, housing situation, employment status, weight, height, number of children) and their child (sex, age, country of birth, school, treatment clinic, additional diagnoses). Questionnaires regarding the child’s diet and physical activity habits, the child’s eating behavior, and parental feeding practices are included in the three assessments. Questionnaires can be answered from a mobile phone/tablet/computer, at a convenient time for the participant. Data regarding number of treatment visits and comorbidities will be collected from the child’s medical journal. Data on implementation outcomes will be collected from parents and HCPs via questionnaires distributed during the study period and semi-structured interviews performed after participation in the ML program. Data from the BORIS registry [55] will be collected retrospectively.

**Table 4 Tab4:** Data collection and time points

TIMEPOINT	Enrollment and randomization	TRIAL PERIOD		
	Pre-intervention	T0	T1	T2
ENROLLMENT:	X			
Eligibility screen	X			
Informed consent	X			
Randomization	X			
INTERVENTION/COMPARATOR:				
* Intervention: More and Less*		X	X	X
* Comparator: Standard care*		X	X	X
* Comparator: Register control*		X	X	X
ASSESSMENTS: Effectiveness outcomes				
* Child’s eating habits*		X	X	X
* Child’s physical activity*		X	X	X
* Child’s eating behavior*		X	X	X
* Parental feeding practices*		X	X	X
* Child’s weight*,* height and waist*		X	X	X
ASSESSMENTS				
* Demographics*		X		
* Adverse events*			X*	X*
* Fidelity*			X	X
* Feasibility*				X
* Acceptability*				X
* Cost*				X

*Data on adverse events is collected continuously. Abbreviations: T0, baseline; T1, 3-month follow-up, T2, 12-month follow-up

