## Discussion

The Co-Fam model combines two evidence-based programs that align with the recommended components for supporting families with children aged 6–12 years, namely being theory-based, focusing on parenting practices and role modelling, and using a person-centered approach, as outlined in the national guidelines for treatment of overweight and obesity in children [25]. Parents exert a key influence on the home-food environment and on the opportunities available for children to be physically active. Thus, support for parents to facilitate healthy habits needs to be strengthened, especially for parents born outside of the Nordic region whose children have a higher prevalence of overweight and obesity than Nordic-born [4]. Furthermore, targeting children before entering puberty has been found to be more effective on future weight development than in older children [23]. Since structured evidence-based parental support programs for children 6–12 years with overweight and obesity are lacking in Swedish healthcare today, many families do not get the recommended support. Thus, if shown to be feasible and effective, the Co-Fam model will provide an evidence-based approach to preventing and treating unhealthy behaviors and overweight and obesity in children [25].

Families with children attending public school in the municipality automatically receive the HSS program, which is integrated into the school’s curriculum and has been successfully delivered since 2022. As the program is delivered during regular classes, families cannot opt out. However, for participation in the ML program, both parents and the child must provide consent. Both parents are encouraged to participate to support consistency in parenting practices. Children will be informed about the study by their parents and asked to consent to the measurements of height, weight and waist circumference which are taken by the school nurse. School nurses are responsible for student health and routinely perform these measurements as part of national follow-ups. Therefore, collecting measurements in this context is considered the least intrusive approach.

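### The ML-versus-register comparison reuses the trial's linear 0-3-12 month slope, although the study does not set when register children are measured; a direct 12-month difference would be safer.

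*Protocol article*

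**What the plan says.** Under Data analysis, the protocol article describes a linear mixed model for BMI z-score at 0, 3 and 12 months with a random intercept per child. Time enters in months, and the treatment-by-time interaction, a change per month, is the effect. The same section then commits the register comparison to this approach, "using the same methods as described above adjusted for confounders".

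The two groups are observed by different routes:

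- **ML arm (Data collection):** the child's "height, weight, and waist circumference will be measured by the school nurse at three timepoints".
- **Register group (Register-based control group):** data come retrospectively from the national child obesity treatment register. Three register children are drawn per ML child with obesity, matched on age, sex, baseline BMI z-score and year of treatment initiation.
- **Visits in standard obesity care:** the control-arm section says that "children with obesity are referred to a pediatrician for yearly check-ups often in combination with follow-up visits to a pediatric nurse". Table 1 recommends at least six visits a year.

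Table 4 lists "Comparator: Register control" with marks at T0, T1 and T2. This row stands in the intervention/comparator block; weight, height and waist have their own row among the assessments.

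The article has a general missing-data clause and defers full detail to an analysis plan that is not shown.

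**The concern.** A straight-line slope summarises a curved course differently depending on when the child is measured. In the randomised comparison both arms share one schedule, so this is common to both. In the register comparison the ML times are planned, while the register times are whatever the register holds. ML puts its ten weekly group sessions in the first three months and then moves to spaced booster sessions, so an early fall followed by a plateau or some regain is plausible. The slope contrast can then show a difference that comes only from visit times.

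A second route to bias is follow-up. ML measurement runs through the school, apart from the sessions. If a later register value requires the family still to be in care, the groups are selected differently after baseline, and matching on baseline values cannot correct that.

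At stake is the national comparison of ML with standard treatment in children with obesity.

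**Working it through.** **The plan's own figure.** The sample size section targets a "difference at 12 months between the groups in BMI z-score of -0.16 with a standard deviation of 0.3, 80% power". With two-sided alpha 0.05 (sidedness is not stated):

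n = 2 × (1.960 + 0.842)² × 0.3² / 0.16² ≈ 55.2, so 56 per arm; 56 / 0.90 = 62.2, so 63 per arm and 126 in total.

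The stated 126 is reproduced. It concerns the randomised trial only; 0.16 serves below as a yardstick. No figure is given for the register comparison.

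**Step 1: visit times, identical true course in both groups.** With complete data at common times, the random-intercept model's slope is the least-squares slope of the mean course. Let y3 and y12 be the mean changes at 3 and 12 months.

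- Times 0, 3, 12: deviations from the mean time are -5, -2, 7 and their squares sum to 78. Slope × 12 = 12 × (-2·y3 + 7·y12) / 78.
- Times 0, 12 or 0, 6, 12: slope × 12 = y12.
- False difference, ML minus register = (4/13) × (y12/4 − y3).

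This is zero on a straight line, where y3 = y12/4. It is positive (against ML) if the fall comes early and negative if it comes late.

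Two assumed courses:

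- *Early fall, then plateau* (y3 = -0.103, y12 = -0.160): (4/13) × (-0.040 + 0.103) = 0.019. The slopes × 12 are -0.141 and -0.160.
- *Fall to -0.16 at 3 months, half regained by 12* (y12 = -0.08): (4/13) × (-0.02 + 0.16) = 0.043. The slopes × 12 are -0.037 and -0.080.

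| Register times (months) | Linear | Plateau | Half regain |
|---|---|---|---|
| 0, 2, 4, 6, 8, 10, 12 | 0.000 | 0.002 | 0.003 |
| 0, 12 or 0, 6, 12 | 0.000 | 0.019 | 0.043 |
| 0, 4, 8 | 0.000 | 0.087 | 0.136 |
| 0, 2, 4, 6 | 0.000 | 0.137 | 0.230 |

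The last two rows suppose that every register series stops early, an extreme case not used for the size below. Against the 0.16 target, 0.019 is 12% and 0.043 is 27%.

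**Step 2: selective loss of the 12-month register value.** Simulation of the random-intercept model with group × time, 150 runs per scenario. Assumed: 32 ML and 96 register children, linear individual courses, SD of 12-month change about 0.3, true difference -0.16 in favour of ML, no loss in ML, all 3-month values present. Simulation error is about 0.3 × √(1/32 + 1/96) / √150 = 0.005. Without loss the estimate is -0.163.

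| Who lacks the 12-month value | 20% missing | 40% missing |
|---|---|---|
| Unrelated to course | -0.155 | -0.165 |
| Poor responders | -0.097 | -0.050 |
| Good responders | -0.226 | -0.284 |
| Those with a worse observed 3-month change | -0.126 | -0.085 |

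In the last scenario, comparing only children with a 12-month value gives -0.111 and -0.057, further from -0.16 than the mixed model. Dropping the earlier values therefore makes matters worse.

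**The case against.** The strongest reply is that the article states none of the conditions that produce bias. It does not say that register BMI is recorded only at clinic visits, that 3-month values are absent, or that children who leave care have no later value. If the six visits a year recommended in Table 1 took place and were recorded, the timing effect would be 0.002 to 0.003. Time is in months, so actual dates can be used; the mixed model keeps children with partial data; there is a missing-data clause; and windows and extraction rules belong in the analysis plan. All of this stands, and it limits the point.

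It does not remove it. The choice of a linear slope for this comparison is already fixed in the article, and actual dates do not cure a straight line fitted to a curved course. Nor did the mixed model remove the bias when loss depended on the observed 3-month change.

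Several stronger readings are tempting but unsupported:

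- *ML will look worse than it is.* The sign of the timing effect follows the shape of the course, and selective loss can run either way.
- *The register mean is the mean of those who stayed in care.* That describes a completer analysis, which is not what is planned.
- *The Discussion shows that families leave care.* Its remark that "many families do not get the recommended support" is explained there by the lack of structured parental programmes and says nothing about leaving.
- *Table 4 promises a 3-month register measurement.* The register row shows the comparator condition and is not a measurement row.

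**Conclusion.** The point holds in a limited form. The article applies a linear 0-3-12 month slope to two groups whose measurement times are set in different ways, so the contrast can depend on visit times. Under assumed non-linear courses, identical in both groups, the false difference is about 0.02 to 0.04 BMI z-score with register values at 0/12 or 0/6/12 months only. It is near zero with visits spread over the year and zero on a straight line.

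Selective follow-up in the register is a further possibility of unknown sign. With 20% to 40% of 12-month register values missing, a true -0.16 was estimated anywhere from -0.050 to -0.284, depending on who was missing. The missing shares, the reasons for loss, the visit times and the group sizes are assumptions, so no single total should be quoted as the bias.

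The comparison is supplementary, non-randomised and confined to children with obesity. The randomised primary analysis and its sample size are untouched.

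**What to change.** For the register comparison only:

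1. Replace the slope with the difference in BMI z-score at 12 months, using the same 12-month window in both groups and modelling time non-linearly or as categories. This addresses visit timing; it does not by itself remove selection.
2. Keep all earlier register values in the model at their actual dates, so that children without a 12-month value still contribute. Do not restrict the analysis to children measured at 12 months.
3. Report, by group, the share with no value in the window.
4. Add a sensitivity analysis that shifts unmeasured children both worse and better, for example by 0.1 and 0.2. If only register children are shifted, the contrast moves by share × shift: with 20% to 40% unmeasured, from 0.2 × 0.1 = 0.02 to 0.4 × 0.2 = 0.08 in each direction.

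The cost is a sentence on the method in the analysis plan, a slightly wider interval and a little more analysis work. No new data are collected.
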